## Abstract

**Background:**

Artificial intelligence tools have the potential to objectively identify youth in need of mental health care. Speech signals have shown promise as a source for predicting various psychiatric conditions and transdiagnostic symptoms.

**Objective:**

We designed a study testing the association between obsessive-compulsive disorder (OCD) diagnosis and symptom severity on vocal features in children and adolescents. Here, we present an analysis plan and statistical report for the study to document our a priori hypotheses and increase the robustness of the findings of our planned study.

**Methods:**

Audio recordings of clinical interviews of 47 children and adolescents with OCD and 17 children and adolescents without a psychiatric diagnosis will be analyzed. Youths were between 8 and 17 years old. We will test the effect of OCD diagnosis on computationally derived scores of vocal activation using ANOVA. To test the effect of OCD severity classifications on the same computationally derived vocal scores, we will perform a logistic regression. Finally, we will attempt to create an improved indicator of OCD severity by refining the model with more relevant labels. Models will be adjusted for age and gender. Model validation strategies are outlined.

**Results:**

Simulated results are presented. The actual results using real data will be presented in future publications.

**Conclusions:**

A major strength of this study is that we will include age and gender in our models to increase classification accuracy. A major challenge is the suboptimal quality of the audio recordings, which are representative of in-the-wild data and a large body of recordings collected during other clinical trials. This preregistered analysis plan and statistical report will increase the validity of the interpretations of the upcoming results.

**International Registered Report Identifier (IRRID):**

DERR1-10.2196/39613

## Introduction

Obsessive-compulsive disorder (OCD) is a chronic, debilitating disorder, which can lower self-esteem, shorten life-expectancy, strain the family, and make it difficult to maintain friendships and attend school [1,2]. First-line treatment for moderate to severe OCD in youth (defined as individuals under age 18 years of age) is cognitive behavioral therapy (CBT) with exposure and response prevention (ERP) [3,4]. During exposure practice, the child tracks the level of distress caused by symptom-provoking stimuli across and within sessions. Here, distress refers to fear, disgust, discomfort, shame, embarrassment, and feelings of incompleteness or emptiness. Monitoring distress provides useful information to clinicians, who use it to plan exposures and help the patient remain mentally present with the exposure [5]. Distress levels also comprise one dimension of the gold-standard measure of symptom severity in OCD. When collected over time, distress can provide information about disease progression and improvement [6]. Frequent measures of distress are essential for understanding mechanisms of change in exposure-based therapies [5]. Self-rated distress may not be frequent enough to discover the processes responsible for therapeutic change, which has led some researchers to code videos of exposure sessions [7]. Behavioral coding is a time-consuming, costly process that is prone to inconsistency and not entirely immune to bias. Ideally, distress would be assessed objectively and affordably in a noninvasive manner.

Objective and automatic psychiatric assessments can be achieved by feeding vocal features into machine learning models. Speech patterns, tempo, volume, and intonation comprise an important part of the overall clinical impression that has been used to diagnose psychiatric disorders for at least 100 years [8]. Speech reflects changes in cognition, affect, motor characteristics, and physiology seen in psychiatric disorders [9]. Voice quality features capture information relating to voice creakiness, harshness, and breathiness [9]. Decreased formant frequencies observed in depressed and anxious speech may reflect dry mouth, decreased articulation, or motor coordination [9].

Vocal features have demonstrated promising results in machine learning for predicting the severity of psychiatric disorders and clinical improvement. A recent review summarized 127 studies that have used automatically extracted speech features to detect the presence or severity of psychiatric disorders [10]. The vocal fold features, jitter, and shimmer were found to be significantly elevated in adults with depression, anxiety, and OCD. Only one study has investigated vocal fold features in OCD. Results from 35 adults suggest that individuals with OCD have voices with more jitter, breathiness, hoarseness and speak at a lower rate than individuals without a psychiatric diagnosis [11]. Increased percent jitter and hoarseness have also been found in children (6-15 years old) with attention-deficit/hyperactivity disorder compared with healthy controls [12].

One major conclusion of the systematic review is that future studies should focus on linking vocal features to specific transdiagnostic problems, such as distress [10]. One study found that self-reported distress and electrodermal activity corresponded with vocal indicators of distress [13]. High levels of cortisol have also been linked to vocal indicators of distress [14]. Another study used audio recordings of 3- to 8-year-old children giving a speech under stressful conditions. The machine learning model classified children with and those without internalizing disorders using vocal features as input with 80% accuracy [15].

The aim of this paper is to increase the robustness of a planned study by documenting our analysis plan of a study with the following objectives: (1) to investigate the correspondence between activation-specific features and OCD diagnosis and severity [16] and (2) to adapt models trained on adult English speech to better align with the target population (Danish speech from children), thus obtaining improved indicators of OCD. In this paper, we also weigh our methodological decisions.

## Methods

### Participants and Setting

We will include audio recordings from a total of 64 youths aged 8 to 17 years (47 with OCD and 17 healthy controls). The audio recordings of diagnostic interviews stem from a large randomized clinical trial and case-control study of OCD, called TECTO [17]—TECTO runs at a public hospital in Denmark.

### Ethics Approval

TECTO and the planned analyses have been approved by the ethics committee of the Capital Region of Denmark (H-18010607). The selection of participants in the current study is depicted in Figure 1.

**Figure 1 figure1:**
[figure not shown]
Flow diagram of audio data selection. OCD: obsessive-compulsive disorder.

### Measures

Trained mental health professionals conducted clinical interviews before inclusion in TECTO to establish diagnoses and OCD severity in patients and rule out psychiatric diagnoses in controls.

#### Diagnostic Status

Trained mental health professionals used a semistructured clinical interview—the Kiddie Schedule for Affective Disorders and Schizophrenia (K-SADS)—to screen for and establish diagnoses in participants [18]. The K-SADS is designed to establish psychiatric diagnoses in youth between the ages of 6 and 18 years.

#### OCD Severity

Trained mental health professionals assessed the clinical severity of OCD using the Children’s Yale-Brown Obsessive Compulsive Scale (CY-BOCS) [19]. The CY-BOCS interview begins with a checklist of obsessions and compulsions to establish which symptoms have been present over the past week. On a scale from 0 to 4, clinicians rate 5 items on the severity of obsessions and 5 items on the severity of compulsions. Severity is rated on 5 dimensions: level of distress caused by the symptoms, functional interference, time consumed by symptoms, and resistance to and degree of control over symptoms. A total severity score is calculated by summing all 10 items on a scale from 0 to 40. Although CY-BOCS scores are continuous, a previous study of 815 youth between the ages of 4 and 18 years found the following cutoff scores to be consistent with global clinical severity ratings: 0-7, subclinical; 8-15, mild; 16-24, moderate; and 25-40, moderate-severe to severe [20]. A CY-BOCS score of ≥16 was required to be included in the study.

### Audio Data Source

Samples of child speech will be taken from the K-SADS interviews. Owing to limited labeled data, we will use the first 10 minutes of the 30- to 90-minute interviews. Audio recordings were obtained using an on-camera microphone of a Sony video camera placed in various positions and in different rooms across observations. Data analysis is outlined in Figure 2.

**Figure 2 figure2:**
[figure not shown]
Overview of the data analysis process.

### Statistical Analysis Plan

The planned study has two main objectives:

Test the usefulness of a previously learned latent model, composed of 2 dimensions representing a compressed vocal feature space guided by activation labels [16], as a marker for OCD diagnosis and severity.Learn a new latent model, which we will propose as an improved candidate indicator of OCD severity.

Our first objective will be achieved through 2 statistical analyses, with the following hypotheses:

Objective 1 (H1): an ANOVA will be conducted to test the first research hypothesis (objective H1A) that there is an effect of diagnosis (OCD vs no psychiatric diagnosis) on the vocal feature latent model. With logistic regression (H1B), we will test hypothesis H1, which states that there is an effect of the vocal feature latent model on OCD severity classifications in moderate to extreme OCD cases, with the vocal feature latent model corrected for age and gender. This analysis will only include patients with OCD, and we will examine the classification accuracy of this model.Objective 2 (H2): the second objective will be achieved through data labeling and machine learning modeling. Here, outcomes will include diagnostic status (OCD vs no psychiatric diagnosis) and OCD severity (CY-BOCS severity scores). We will validate the modeling using a leave-two-individuals-out cross-validation and prediction accuracies. Subsequently, we will assess the obtained results using an independent test. We will extract data from 10 of the youths’ audio samples post machine learning modeling for this purpose.

### Processing Pipeline

#### Preprocessing Audio and Annotations

The audio preprocessing system is illustrated in Figure 3. To effectively use the audio signals, the audio recordings must be segmented into shorter segments. Next, speech and nonspeech regions must be differentiated. To obtain speaker segments, the conversations will first be segmented into speech and nonspeech regions.

We will use pretrained voice activation and diarization models that will be fine-tuned with a few manually annotated ground-truth labels of speech and nonspeech samples from our data set [21]. We follow this approach to ensure a balance between resources spent in training a model while maintaining high accuracy in the obtained speaker segments. Following speaker segmentation of the audio recordings, only the audio segments corresponding to the youth are retained.

**Figure 3 figure3:**
[figure not shown]
Flow diagram of the preprocessing pipeline.

#### Pretrained Segmentation and Diarization Model

We used the vad-crdnn-libriparty pretrained model from SpeechBrain for speech detection [22] owing to its flexibility and modular structure, which is a favorable quality when applying models to clinical data owing to the tractability of errors. The pretrained model is based on a combination of convolutional and recurrent neural networks and a fully connected network. The model accepts audio segments as input and yields a posterior probability frame-level or segment-level posterior probability as output. Finally, a threshold is applied on the output posterior probability to classify the segments as speech and nonspeech.

We define a speaker segment to be an utterance of 2-4 seconds from a youth. The interviews will have a varying number of utterances. For a balanced analysis, we will randomly select 10 speaker segments per youth. Since the random selection of speaker segments may result in a high variance within the observations, we will also explore the feasibility of analyzing specific audio segments consistently over all speakers. These audio segments will be selected on the basis of insightful segments in the interview; for instance, questions in the interview associated with depression. In total, 10 interviews—5 with youth with OCD and 5 with those with no psychiatric diagnosis—have already been used to develop an appropriate method for speaker segmentation [21]. We will add the remaining 54 observations once we commence the described analysis.

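### Objective 1 discards all but 10 randomly drawn segments per youth for a balance its models do not need, which costs precision and ties the result to one draw

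*Protocol article*

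**What the plan says.** The section Audio Data Source limits the material to an opening window: "Owing to limited labeled data, we will use the first 10 minutes of the 30- to 90-minute interviews". The section Pretrained Segmentation and Diarization Model then defines the unit, "We define a speaker segment to be an utterance of 2-4 seconds from a youth", notes that "The interviews will have a varying number of utterances", and sets the cap: "For a balanced analysis, we will randomly select 10 speaker segments per youth".

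The 10 segments feed both Objective 1 analyses. Under Statistical Models for Objective H1A they are the repeated measures of 64 youths (10 × 64 = 640 rows) in a mixed model with youth as a random effect. Under Adjusting for Confounding and Calculating Average Features they are averaged per youth, with a divisor of 10, to give the H1B predictors.

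The article sees a drawback: "Since the random selection of speaker segments may result in a high variance within the observations". Its response is that "we will also explore the feasibility of analyzing specific audio segments consistently over all speakers", with this selection rule: "These audio segments will be selected on the basis of insightful segments in the interview; for instance, questions in the interview associated with depression".

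Adjusting for Multiple Testing defines a family of four P values, each tested at 1.25%. It names no test on the content-selected segments.

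**The concern.** The reason given for the cap does not fit the models. A mixed model with a random youth effect accepts unequal numbers of segments, and a youth mean can be taken over any number. The further segments are already there: Preprocessing Audio and Annotations retains all of the youth's segments before the draw, and under Audio Features v1 and v2 come from OpenSmile features passed through a pretrained network. Human activation ratings are needed only for Objective 2.

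What is at stake is precision in a comparison of 47 patients with 17 controls, a study whose Limitations section already names the small sample as a type II error risk. A verdict at 1.25% could also change had another 10 segments been drawn. In addition, the article does not say what weight the content-selected segments would carry next to the random ones.

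**Working it through.** **The article's own figure.** 0.05/4 = 0.0125, as stated. Four tests at that level have a Bonferroni bound of 5.0%, or 1 − 0.9875⁴ = 4.9% if independent. The article gives no power calculation to reproduce.

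**Inputs.** Segments kept: m = 10. Groups: 47 and 17. Two inputs are not in the article and are assumed: the number of eligible segments per youth (50, with a range of 40 to 80) and the intraclass correlation, ICC (0.1 to 0.5). Table 2 would give 2.29/(2.29 + 2.33) = 0.50, but it is labelled as simulated, so it is not evidence on the real ICC.

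**Precision.** With total variance 1, the variance of a youth mean over m segments is ICC + (1 − ICC)/m.

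| ICC | m = 10 | m = 50 | Ratio | Fall in SE with 50 |
|---|---|---|---|---|
| 0.2 | 0.2 + 0.8/10 = 0.280 | 0.2 + 0.8/50 = 0.216 | 1.30 | 12% |
| 0.3 | 0.3 + 0.7/10 = 0.370 | 0.3 + 0.7/50 = 0.314 | 1.18 | 8% |
| 0.5 | 0.5 + 0.5/10 = 0.550 | 0.5 + 0.5/50 = 0.510 | 1.08 | 4% |

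The last column is 1 − √(variance at 50 / variance at 10). With 80 segments available, the standard error of the 47-versus-17 contrast would fall by about 23%, 13% and 4% at ICC 0.1, 0.2 and 0.5.

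**Dependence on the draw.** If two sets of 10 are drawn from M available segments, their test statistics correlate at [ICC + (1 − ICC)/M] / [ICC + (1 − ICC)/10]. For example, ICC 0.2 and M = 80 give 0.210/0.280 = 0.75. Simulation at two-sided 1.25%, ignoring the age and gender terms, with M = 40 to 80:

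| ICC | Correlation of two draws | Opposite verdicts at 50% power | At 80% power |
|---|---|---|---|
| 0.1 | 0.59–0.65 | 28–30% | 19–21% |
| 0.2 | 0.75–0.79 | 21–23% | 15–16% |
| 0.3 | 0.83–0.86 | 17–19% | 12–13% |
| 0.5 | 0.92–0.93 | 12–13% | 8–9% |

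**Type I error of a single draw.** Simulated at 0.0124 to 0.0126 per test against a nominal 0.0125, so there is no inflation.

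**Conditional case.** Suppose the content-selected segments were tested on the same four hypotheses at 1.25%, and either set could carry the conclusion. The Bonferroni bound would be 8 × 0.0125 = 10%. Independent tests give 1 − 0.9875⁸ = 9.6%. Correlation of 0.5 or 0.9 between the sets gives 9.1% or 7.2%.

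**Downside of using all segments.** In the mixed model a youth's weight is roughly the inverse of the variance above. With 80 against 20 segments, the weights stand at (0.2 + 0.8/20)/(0.2 + 0.8/80) = 0.240/0.210 = 1.14 at ICC 0.2, and (0.1 + 0.9/20)/(0.1 + 0.9/80) = 0.145/0.111 = 1.30 at ICC 0.1.

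**The case against.** A prespecified random sample of fixed size is a valid design: it is unbiased and holds its error rate. That stands. The loss depends on inputs the article does not give, and at an ICC of 0.5 it is small. Verdicts flip often only when the true effect lies near the decision boundary. That stands too.

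Equal numbers also protect against informative segment counts. The Introduction cites a study in which adults with OCD spoke at a lower rate, so the amount of speech might differ by group. With all segments, talkative youths would weigh more in the mixed model and in the age and gender regression, and H1B predictors would differ in precision. This is a fair caution. The weight ratios above suggest it is modest, and an equally weighted analysis can check it.

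The Limitations section calls preprocessing and labelling time-consuming. Labelling does not enter Objective 1, and speaker segmentation precedes the draw, so little of that burden bears on the cap.

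Several stronger readings are tempting but unsupported:

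- A reader might infer a second set of tests outside the error control. The article describes a feasibility exploration and attaches no hypothesis, P value or decision rule to it.
- A reader might infer that segments are hand-picked after listening. The text says the same segments are used for all speakers and gives interview questions as its example.
- A reader might take the shortage of labelled data as the reason for the cap. It is given for the 10-minute window; the reason for 10 segments is balance.

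**Conclusion.** The point holds as one of efficiency and reproducibility, not of validity. The cap removes usable data for a balance that H1A and H1B do not require. If 50 segments were available, the variance of a youth mean would be about 30%, 18% or 8% larger than necessary at ICC 0.2, 0.3 or 0.5. The outcome would also depend to some degree on which segments were drawn. The segment count and ICC are assumptions: a low ICC makes the loss material, a high one makes it slight.

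The article does not plan a breach of the 5% family-wise error. A rise to about 7–10% would follow only if the content-selected segments were tested at 1.25% and either set were allowed to decide. One sentence fixing their status removes that possibility.

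**What to change.** 1. For H1A, fit the mixed model to all eligible 2–4 s youth segments from the first 10 minutes. For H1B, average over all of them, replacing the divisor of 10 by each youth's own count.
2. As a sensitivity analysis in case segment counts differ between groups, add an equally weighted youth-mean analysis or the draw of 10 with a fixed seed.
3. Keep the 10-segment sample for the annotated Objective 2 data, where human rating is the limit.
4. State that any analysis of content-selected segments is exploratory and outside the four-test family.

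The cost is a little more computing and a few sentences of text. The small downside is that youths who talk more carry somewhat more weight in the mixed model, which step 2 addresses.

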#### Audio Features

From each speaker segment, we will extract the extended Geneva minimalistic acoustic parameter set [23], consisting of functionals of lower-level features. We will use the OpenSmile toolkit to extract these features and the resulting feature vector has a length of 88 [24].

The derived feature vector will be used as input to a neural network autoencoder model to obtain a latent model. The latent model is pretrained on English speech using the Interactive Emotional Dyadic Motion Capture data set and a semisupervised loss as previously described [16]. The latent model is a 2D latent space (*v*1 and *v*2) in a semisupervised denoising autoencoder with a reconstruction loss plus a loss based on the linear association between the activation labels and the latent space (the aim is a high association). Thus, to obtain *v*1 and *v*2, the 88 vocal features are projected into the latent space through the pretrained network. Previous analyses indicate that this latent space represents 2 dimensions of speech activation or intensity [16]. Sad and bored speech is characterized by low activation whereas elated and angry speech is characterized by high activation [25]. Thus, we assume that this latent space represents emotional intensity. We do not have an objective metric to evaluate this quantitatively using the current data and labels. Therefore, we will test this assumption in future work when more data labels are available. 

For the machine learning analyses, we will use the raw speech signals to learn new features.

### Statistical Models

Let *v*1 and *v*2 describe the vocal feature latent model adjusted for age and gender effects.

#### Statistical Models for Objective H1A

We will perform an ANOVA using a mixed effects regression model with the vocal features *v*1 and *v*2 as the outcome. We code the diagnosis, *Diagnosis*={0, 1} for no-OCD or OCD, respectively. The model for the *j*th vocal feature is as follows:

*v_ij_* = *μ_j_* + *α_j_*(*age_i_*) + *γ_j_*(*gender_ii_*) + *v_j_*(*age* × *gender*)*_i_* + *δ_j_*(*Diagnosis_i_*) + *y_j_*(*youth_i_*) + *ε_ij_* (1)

where *μ_j_* is a constant offset for the *j*th endpoint, *i* = 1, ..., 200, *y_j_* (*youth*_i_) ∼ *N* (0, *σ*^2^*_yj_* ), *ε_i_* ∼ *N* (0, *σ^2^_j_*), and the effects are mutually independent. Age, gender, and an interaction between age and gender are included as fixed effects to remove confounding effects from these variables. Diagnosis is included as a fixed effect and is our primary interest. The individual youth, denoted *youth*, is included as a random effect. *Diagnosis* is included as a fixed effect. In total, 10 repeated measures are available for each of the 64 youths included in this model.

With this analysis, we shall test the hypothesis that there is no effect of diagnosis; that is, *H*_0_ : *δ_j_* = 0, or equivalently that the means of the vocal features are equal for the OCD and no-OCD groups (when effects of age and gender are removed), at a 1.25% level of significance.

